#### Primary outcome

PD-specific quality of life will be recorded using the PDQ-8 (Parkinson’s Disease Questionnaire, German version). It contains 8 questions rated on a five-point scale assessing aspects of mobility, everyday activities, emotional well-being, stigma, social support, cognition, communication, and physical discomfort. High values indicate low quality of life. It is a valid and reliable instrument for measuring the quality of life in people with PD [24].

#### Secondary outcomes

*Participation restrictions* will be recorded with the IMET. This ICF-oriented [25] instrument determines the subjective impairment of chronically ill people in everyday life. It surveys restrictions on participation in nine everyday areas using a scale from 0 to 10 and can be evaluated both at the individual item level and as a total score. High values indicate high participation restrictions. The IMET has proven valid and reliable for use in chronically ill patients [26, 27].

*Falling anxiety* will be measured with the German version of the Falls Efficacy Scale International Version (FES-I). The questionnaire consists of 16 items rated on a four-point scale, which are combined into a total score. High values indicate high fear of falling. Several studies have reported this instrument’s high reliability and validity [28].

*Sleep problems* will be measured with the German version of the Parkinson’s Disease Sleep Scale (PDSS-2). The scale contains 15 questions rated on a five-point scale that address PD-specific sleep disorders. The items are summarized in a sum scale. High values indicate a high level of sleep disturbances. Reliability and validity can be considered good [29].

To assess *anxiety and depression*, the short version of the Health Questionnaire for Patients (PHQ-4) will be used. The questionnaire captures anxiety and depression with two questions each that are rated on a four-point scale. Sum scores are calculated, and higher values imply higher levels of anxiety and/or depression. Reliability and validity are considered good [30, 31].

*Comorbidity* will be measured by a modified version of the comorbidity questionnaire of Sangha [32], which includes total of 14 diseases that are recorded dichotomously.

The severity of *pain* in different parts of the body will be assessed on a five-point scale [33].

*Performance capability* in the domains of work, everyday life and leisure is quantified using numerical scales from 0 to 10, with high values indicating high performance. The three items have been shown in routine surveys to be a valid method for determining performance limitations [34, 35]. *Physical activity* is measured using the instrument used by Mensink in the 1999 Federal Health Survey [36]. *Sociodemographic data* will be assessed using single items [37].

### B: qualitative measures

#### Interviews and focus groups with patients, therapists and doctors

Patient experiences with the tablet-based training programme will be assessed in four focus groups of PD patients at the end of the MKP. The particular focus will be on the personal use and manageability of the app, the satisfaction with the patient-centred seminars and the individually created training plan. In addition, qualitative individual interviews with 16 patients after MKP will be carried out. The interviews will take place twice: The first time at week 9 and the second time at week 36 after the MKP, when the patients will come to the clinic for their onsite check-up. They will focus on the feasibility of implementing the individualized training plan at home; on satisfaction with the app, the phone calls and the personal appointments in the clinic; and on the adjustments to the training programme. In addition, the wishes and needs of the patients with regard to further development or optimization of the training programme and app will be recorded. To achieve a sample composition that is as heterogeneous as possible [38], patients of different genders and with different degrees of disease severity, education and extent of physical activity will be recruited prior to the MKP for the interviews. The perspective of doctors and therapists will be taken into account by means of a focus group with the specialist staff of the clinic. This focus group will take place at the end of the recruitment process in the clinic and will address the assessment of the patients’ use of the tablet-based training programme during inpatient treatment from a medical and therapeutic point of view. In particular, the practicality of the app for the patients and an assessment of the extent to which the app supports the therapeutic and medical work during the MKP and the preparation for the time at home will be in the foreground. In addition, individual interviews will be conducted after the MKP with the physiotherapist responsible for PD patients. These interviews will concern the practicality of evaluating the data with the help of the cockpit, the telephone calls and the feasibility of adapting the training programmes. All interviews and focus groups will be conducted on a guided basis. Both the guidelines and the results of the interviews will be presented and discussed among the project team and in an interdisciplinary expert forum (“Qualitative Methods Working Group”, AQUAM). The interviews will take approximately 30 min, and the focus groups will take longer. After the participants have given their consent, all interviews and focus groups will be recorded digitally and transcribed literally. The evaluation will be based on the method of qualitative content analysis [39, 40].

### C: formative evaluation of the tablet-based training programme and the administration panel (cockpit)

The formative evaluation will examine the usability of the app and the cockpit during app development. The evaluation will take place at the Usability Laboratory of the Institute for Multimedia and Interactive Systems. For this purpose, prototypes of the app and the cockpit will be developed, and potential users (PD patients) will be asked to perform sample tasks, such as playing a training video, with the prototypes. To evaluate the app, methods that gather both objective data (processing time and accuracy, human error, mental load, finding weak points) and subjective data on satisfaction and acceptance (e.g., QUIS [41], UTAUT [42]) and mental stress (NASA-TLX [43]) will be combined.

Positively evaluated design aspects will flow into the development of the overall system. At the end of the intervention, the tablet-based training programme will be evaluated by the PD patients, and the cockpit will be evaluated by the physiotherapist. The evaluation of the usability of the app and the cockpit will be based on the ISONORM questionnaire [44], which covers the implementation of the dialogue criteria by means of 21 items based on the International Ergonomics Standard DIN EN ISO 9241-110. In addition to the quality characteristic of suitability for use, subjective factors of use will be taken into account. For this purpose, the AttrakDiff questionnaire [45] will be used to measure the perceived hedonic and pragmatic quality.

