### Case number calculation / sample size

With regard to the changes in the primary outcome, we assume that both groups (the CG and IG) will have improved in a similar way at the end of the MKP. According to our assumptions, the effect of the CG during the subsequent period will approach the starting level again, while the positive changes in the IG will stabilize or even increase slightly. To estimate the required sample size, we have referred to the results of existing studies on the influence of physical activity on quality of life (PDQ-8) in PD patients. For the effect determination, the data of Ebersbach et al. [46], Morris et al. [47] and Nadeau et al. [10] are being consulted. In Ebersbach et al., the quality of life over a 4-month course showed effect sizes of average magnitude (ES = 0.47) for patients who underwent physical training (Nordic walking), whereas there was no change in the CG. Morris et al. also report a significantly improved quality of life, with a mean effect size of ES = 0.45, after muscle training over a 3-month span. In their controlled study on the effect of intensive treadmill training (speed and incline) on quality of life, Nadeau et al. found an effect size of ES = 0.73 over a 6-month course; for simple treadmill training, they found an effect strength of ES = 0.21. In the CG, the quality of life did not change. For the calculation of the number of cases, we assume that participation in the tablet-based training programme (IG) will lead to clinically relevant positive effects (t_0_ vs. t_2_ ES = 0.40) on quality of life (PDQ-8) 9 months after the end of MKP. In contrast to the IG, there will be no changes in the CG at t_2_. To demonstrate differences between the IG and CG 9 months after MKP on the order of at least ES = 0.4 with two-sided testing at α = 5% and a power of 80%, a group size of *N* = 100 net is required for each IG and CG. We expect only a moderate dropout rate of 25% among patients after MKP due to their attachment to the clinic. Thus, to be able to evaluate N = 100 patients per group, 133 participants per study group must initially be included. Approximately 120 PD patients participate in the MKP per quarter at the partner clinic. Based on the defined inclusion and exclusion criteria, we expect 70 patients per quarter to be included in the study. The recruiting of the CG and IG will take place over a period of nine months each. Taking into account a rate of study refusal of 25%, the targeted number of cases in the clinic can be recruited within this time frame.

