### Immediate expected results of the project

Through the personalized training programme, we expect an increase in physical activity that positively affects the motor and non-motor impairments of PD patients and thus improves quality of life. Due to the regular supervision and adaptation of the training programme, we assume that the positive effects of MKP can be maintained longer and that a slowing down of the course of the disease can be achieved. Due to the high proportion of self-performed physically activating exercises and physical activity in our intervention, individualized, time-consuming care by a therapist can be significantly reduced. It can be assumed that costs can significantly be saved in comparison to conventional occupational and/or physiotherapy prescriptions. The physical and everyday obstacles that PD patients face in executing and maintaining physical activity are considered in our individual training plan and in the preparatory and accompanying measures (such as patient-centred seminars and telephone and in-person support). Thus, the intervention meets the specific needs and requirements of this particular patient clientele and should therefore achieve high acceptance and adherence.

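### Usability is rated at the end of the intervention and home feasibility is asked at clinic visits, with no stated measurement point for patients who stop, so these results are likely to be selected towards those who stay

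*Protocol article*

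**What the plan says.** Three parts of the protocol article fix when trial patients give their view of the programme.

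- **Section C (formative evaluation), end rating.** "At the end of the intervention, the tablet-based training programme will be evaluated by the PD patients". The instruments are the ISONORM, with 21 items, and the AttrakDiff: "The evaluation of the usability of the app and the cockpit will be based on the ISONORM questionnaire". No earlier questionnaire rating of the finished app by trial patients is stated. The earlier work in this section is laboratory testing of prototypes, in which "potential users (PD patients) will be asked to perform sample tasks".
- **Section B, interviews.** Sixteen patients, chosen before the MKP to be as varied as possible, are interviewed twice about feasibility at home and satisfaction with the app, calls and visits. The first interview is at week 9, and "the second time at week 36 after the MKP, when the patients will come to the clinic for their onsite check-up".
- **Section B, focus groups.** "Patient experiences with the tablet-based training programme will be assessed in four focus groups of PD patients at the end of the MKP". On content: "The particular focus will be on the personal use and manageability of the app". They take place before the home phase.

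The sample size section says: "We expect only a moderate dropout rate of 25% among patients after MKP".

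Other data on use accrue during the home phase. Under Intervention, patients document problems after each scheduled session and rate well-being, effort and fun, while the physiotherapist monitors adherence and telephones. Section D analyses planned against performed activity, reasons for postponing and the content of calls. The section on cockpit data describes usage statistics by patient and across patients.

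**The concern.** Both instruments that ask patients how the programme worked at home sit at points that a patient reaches by staying: the end of the intervention and the on-site check-ups. A patient who gives up at month three because the app or the effort did not suit can tell the team most about feasibility, yet no contact is stated at which this view would be collected.

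At stake is the interpretation of parts B and C. The abstract names feasibility and acceptance as the purpose of the qualitative part. The discussion already expects that the intervention "should therefore achieve high acceptance and adherence" and looks ahead to transfer to other clinics. A clinic deciding whether to adopt the programme needs to know why patients stop, and a rating by those who remain cannot tell it. The point concerns the single-group usability and feasibility results only.

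**Working it through.** **1. The plan's own figure.** Inputs from the sample size section: standardised difference 0.4, two-sided α of 5%, power 80%, dropout 25%.

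- Per group, normal approximation: 2 × (1.960 + 0.842)² / 0.4² = 98.1, so 99. The t-test version gives 99.08, so 100. Power at 100 per group is 0.807.
- Inflation: 100 / 0.75 = 133.3. The article states 133 (134 if rounded up).

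The figure reproduces. It is also the only source in the document for the number who may be lost.

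**2. Who may miss the end rating.** 133 × 0.25 = 33.25, about 33 intervention patients, *if* every study dropout also fails to give the rating. That condition is an assumption.

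**3. Who may miss the interviews.** *If* the 25% applies to the 16 interviewees, 16 × 0.25 = 4 are expected to be lost by week 36. The chance of losing at least one is 1 − 0.75¹⁶ = 0.99. The chance of losing at least three is 0.80 (binomial).

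**4. Possible effect on a reported rating.** Let *d* be the share not rated, *s* the mean rating of stayers and *l* that of leavers. The mean among all users is (1 − *d*)*s* + *d l*, so the reported figure exceeds it by *d*(*s* − *l*). At *d* = 0.25 the excess is a quarter of the gap between stayers and leavers.

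For illustration, suppose that 80% of stayers find the app acceptable. This is an assumption: the article plans no such proportion and defines no threshold.

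| Assumed acceptance among leavers | All users, *d* = 25% | Excess of the stayers' 80% |
|---|---|---|
| 0% | 0.75 × 80 + 0.25 × 0 = 60.0% | 20.0 points |
| 25% | 60 + 6.25 = 66.3% | 13.8 points |
| 50% | 60 + 12.5 = 72.5% | 7.5 points |
| 80% (same as stayers) | 60 + 20 = 80.0% | 0 points |

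With an assumed loss of 10% the range is 0 to 8 points, and with 40% it is 0 to 32 points. These figures show how the excess depends on the inputs. They do not estimate it.

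**5. Whether another source fills the gap.**

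| Source | What it gives | What it does not give |
|---|---|---|
| Laboratory tests (section C) | Usability of prototypes on sample tasks | Experience at home |
| Focus groups (section B) | Use and manageability during the MKP | Anything after discharge |
| Session ratings (Intervention) | Problems, well-being, effort and fun up to the last documented session | A usability rating; reasons for quitting |
| Calls and postponements (section D) | Patients' needs; reasons for moving a session | A usability instrument; stated reasons for leaving the programme |
| Cockpit statistics | Frequency, duration and broken-off videos | Why use fell |

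These sources can show that use is falling. None is described as giving a leaver's usability rating or reasons for leaving.

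**The case against.** The strongest case against has four parts.

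- **Leavers are not silent.** Session ratings, calls and cockpit data accrue up to the moment of stopping and do not depend on clinic attendance. Interviewees are chosen before the MKP, so the choice itself cannot favour those who persist, and the first interview comes as early as week 9. Travel to the clinic is reimbursed. All of this stands. A reader might infer that patients who give up are not heard at all; the documents do not support that.
- **No passage excludes stoppers.** Section C speaks simply of the patients, and someone who has stopped training may still attend a visit or return a form. This also stands. Selection is a likely consequence of the timing, not a stated rule.
- **The 25% is not an abandonment rate.** It is study dropout, used to size both groups for the PDQ-8. Some dropouts will leave for reasons unrelated to the app. A reader might go further and conclude that acceptance is overstated by a definite number of points. No proportion finding the app acceptable is planned and no rating for leavers is available, so no such figure can be given.
- **The article is condensed.** Handling of discontinued patients may be in the full protocol, and rating a programme at its end is an ordinary choice. The first part is fair. The point nevertheless rests on timings that the article does state, and these can be improved whatever the full protocol adds.

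**Conclusion.** The point holds as a limited design weakness. The stated timings make it likely that the end-of-intervention ratings and the later interviews are selected towards patients who stay, and the results may favour the app. The direction is likely but not certain. The size cannot be derived from the documents and could be zero. If all of the expected 25% go unrated, it is a quarter of the difference in rating between stayers and leavers.

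The conclusion assumes that study dropout is related both to not giving a rating and to how the app would have been rated. The documents neither state nor rule out either link.

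The primary PDQ-8 comparison and the sample size are not affected. The change is worth making because it is cheap and because a leaver's view at the time of stopping cannot be recovered later.

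**What to change.** In section C, give the ISONORM and AttrakDiff when a patient stops the programme or returns the tablet, whichever comes first, and otherwise at the end of the intervention.

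In section B, if one of the 16 interview patients does not come to the week 9 or week 36 visit, hold that interview by telephone.

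In the report, show ratings separately for those who stopped and those who stayed, each with length of use. State how many intervention patients gave no rating, and summarise their cockpit usage data.

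**Cost.** The instruments and the 16 interviewees stay the same, and telephone contact is already part of the programme. The addition is one contact with each patient who leaves. Some will decline it, which is why the number of non-raters must be reported. Ratings after a few weeks will stand beside ratings after nine months, so the two groups should not be pooled without showing length of use.

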### D: evaluation of the training programme’s implementation

In addition to surveying practicality and satisfaction with the app (Section B), the training programme will be evaluated with regard to its content. For this, the planned and performed physical activities, the percentage of achieved repetition numbers, the adjustments to the training plan and the reasons for postponing scheduled appointments will be analysed. Additionally, the content of the telephone calls will be analysed to gain deeper insight into the specific needs of the patients.

### Data management

#### Patient documentation

For the uniform organization and documentation of the flow of subjects in the clinic, an automated Excel documentation file will be generated, and the person responsible for the study will be trained to use it before the recruitment process begins. Each patient will be assigned a four-digit identification number (ID) (pseudonymisation of the data). The first digit will encode the assignment to the IG or CG, and the subsequent digits indicate the number of recruited respondents. All personal data will be documented on a separate data sheet in an Excel file. A corresponding link will be made via the ID. Before transferring the data to the Institute for Social Medicine and Epidemiology, these personal data will be deleted. The collection of these data will take place exclusively in the clinic for standardized documentation. The collection and storage of the data from the questionnaires will be performed separately.

### Data entry and control

The entry of data from the questionnaires in the quantitative study part (A) will be carried out by a student assistant under the guidance of a scientific employee. The entered data will be checked for random double entries (5–10%) by examining their validity and plausibility.

### Data monitoring

It is a non-drug study investigating the health benefits by a training programme fitted to the individual abilities of the patients. Therefore, harmful or adverse events are not expected. Because it is a study with minimal to no risks, there is no need of a data monitoring committee. An interim analysis is not planned.

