## Background

Parkinson’s Disease (PD) is one of the most common neurodegenerative diseases [1] with an onset usually at 65 to 70 years of age [2]. An increase in the number of affected people is expected [3]. In addition to the serious physical and mental suffering of those patients, the disease represents a heavy financial burden on the German health care system [4], and the total annual costs in Germany are currently approximately 2.8 billion euros [5]. Of this, 70% is attributable to direct medical expenses, which consist of medication costs and inpatient treatment [4]. The number of patients treated with a Parkinson’s complex treatment (Multimodale Komplexbehandlung bei Morbus Parkinson, MKP) according to OPS 8-97d has risen sharply in the last five years [6]. Further costs arise from occupational and physiotherapeutic treatments, among others [7]. Physical activity is of considerable importance to disease progression. Training practices such as physiotherapy and various physical activities (including Nordic walking, Tai Chi, dancing, strength training, treadmill training) have a positive impact on gait, endurance, strength, balance, and quality of life for patients [8–12]. The S3 guideline “Idiopathic Parkinson’s Syndrome” recommends physiotherapy, including other physical activities, as a flexible and long-term treatment strategy. A basic principle is to motivate patients to participate in regular, adaptive physical activity [13]. This is made more difficult not only by motor restrictions (rigor, akinesia) but also by non-motor symptoms. Anhedonia (joylessness), apathy, and possibly depression symptoms often present in many patients are factors that hinder an active lifestyle. The inpatient MKP includes both drug therapy and intensified activating therapy that includes physiotherapy and occupational therapy, among other treatments. MKP improves the overall condition and quality of life of PD patients in many cases [14]. After discharge, however, there is often a lack of the human resources and structures in the outpatient sector that are needed for the necessary interprofessional treatment of the disease [14]. There are almost no physiotherapists with a main focus on PD. Therefore, patients rarely receive PD-specific outpatient physiotherapy care following MKP that builds on the physically activating exercises and on the achieved results of MKP. The aim of this intervention is to achieve largely autonomous initiation and maintenance of physical activity in PD patients.

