During MKP, after completing an exercise, patients record the repetition rate or duration of the exercises on the tablet and rate them with regard to well-being, effort and fun. During the MKP, patients also take part in two patient-centred seminars. The first is primarily for acquiring knowledge and motivation. The focus of the second seminar is on preparing for everyday life at home. Each patient considers personal barriers that may arise in daily routine and strategies to overcome those barriers. Possible action alternatives are defined and entered into the app. At an individual appointment at the end of the MKP, patients plan their personal home training programme on the tablet, with the support of the physiotherapist. The patient chooses exercises that match their abilities, needs and preferences. The physiotherapist assists the patient in putting together their individual training programme: she gives advice regarding the selection of the activating exercises, the degree of difficulty and the number of repetitions. The exercises and the adaptation of the exercises over the weeks are based on the learning method of behaviour shaping in operant conditioning. Here, the desired motor behavioural goal is achieved by gradually increasing effort and difficulty, practising repetitive exercises and constantly adjusting the exercises to the patient’s level of ability. Shaping has proven to be an effective training method in neurological movement disorders [18]. Patients will set a date and time for at least three 30-min sessions of physiotherapy exercises and for at least one physical activity per week for the next three weeks at home. The app displays this individually scheduled training programme in a calendar function. At home, the app reminds patients through a sound signal and/or push notification to execute their exercise programme at the scheduled time. Postponing a session (e.g., due to temporary aggravation of motor impairments, so-called off periods) is possible. The videos offer visual support in the execution of the selected exercises. After completing a scheduled training session, patients will document whether the given repetition number or duration was achieved and whether there were problems performing the exercises, and they also rate the activity in terms of well-being, effort and fun. After the end of the MKP, the data are transferred automatically from the app into an administration panel called “Cockpit” at the clinic. There, the supervising physiotherapist can monitor adherence by controlling the patient’s documentation regarding the execution of the exercises and activities, the repetition number, incomplete video viewings, etc. To permit this, the app transmits the gathered statistics for the activities performed by the patients at regular intervals. To be independent of wireless Internet access, transmission takes place via the mobile network. Based on these data, the physiotherapist provides feedback by phone and adjusts the training programme at regular intervals after the end of the MKP. Because PD patients are prone to small movement amplitudes during exercise that they cannot perceive and therefore cannot correct by themselves, regular correction by experts is required. For this reason, in addition to the telephone contacts, the patients visit the clinic four times after their MKP. Travel expenses to the clinic will be financially reimbursed. If patients have any further need for assistance between those pre-defined appointments, they can contact their physiotherapist at the hospital. Regular, attentive care and feedback from the physiotherapist promote long-term adherence [19].

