## Methods

### Eligibility criteria

All patients admitted to our partner clinic for a three-week MKP with a diagnosis of idiopathic Parkinson’s syndrome will be eligible to participate (ICD G20.0 and G20.1). Concomitant care and interventions as e.g. privately organized physiotherapy sessions after the MKP are allowed.

Exclusion criteria: Montreal Cognitive Assessment (MoCA) < 18 points, Berg Balance Scale < 41 points, a major depressive episode, moderate to severe dementia, and cardiovascular and orthopaedic/surgical reasons that argue against independent home training. Participants will be also excluded from the study if they are being admitted to an acute hospital during their MKP.

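### The statement that adverse events are not expected is weakly justified, and the listed outcomes would give no comparable data on falls and injuries in the two groups

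*Protocol article*

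**What the plan says.** The Data monitoring section of the protocol article starts from the nature of the intervention: "It is a non-drug study investigating the health benefits by a training programme fitted to the individual abilities of the patients". It then draws the conclusion: "Therefore, harmful or adverse events are not expected". On oversight it adds: "Because it is a study with minimal to no risks, there is no need of a data monitoring committee".

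Other sections describe the programme and its population:

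- **Background:** "The aim of this intervention is to achieve largely autonomous initiation and maintenance of physical activity in PD patients".
- **Intervention:** for the first weeks at home, patients schedule "at least three 30-min sessions of physiotherapy exercises and for at least one physical activity per week". The IG programme runs for nine months after the inpatient treatment (MKP). It is accompanied by remote monitoring of app data, phone feedback, four clinic visits and contact with the physiotherapist on request.
- **Eligibility criteria:** patients with a Berg Balance Scale score below 41 are excluded, as are those with "cardiovascular and orthopaedic/surgical reasons that argue against independent home training".
- **Table 1:** fear of falling (FES-I) is a secondary outcome. No item on falls, injuries or adverse events is listed. Health-service use, including treatments, hospital stays and medication, is collected at t0 and t2 as a moderating variable.
- **Limitations:** the only patient-level risk named is worsening of the disease.

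**The concern.** The absence of a drug does not imply the absence of harm. For exercise at home in Parkinson's disease the foreseeable harms are falls and exercise injuries, and the eligibility criteria show that the authors had physical risk in mind. Screening and tailoring are reasons to expect a low risk, not reasons to expect none.

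The statement matters because of what surrounds it. Fear of falling cannot stand in for falls: a patient who becomes more confident and more active may fear falling less and fall more. After discharge the two groups also differ in how easily an event reaches the study team. Any harm data that emerge informally would therefore not be comparable.

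The article looks ahead to use in other clinics and, under its expected results, to less therapist time: "Due to the high proportion of self-performed physically activating exercises and physical activity in our intervention". Anyone taking the programme over will ask whether patients fell or were injured more often than under usual care. The listed instruments would not answer that.

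**Working it through.** **1. The plan's own figure.** The sample size is not in dispute. For ES = 0.4, two-sided 5% and 80% power, n = 2 × (1.960 + 0.842)² / 0.4² = 98.1, or 99 per group. The t-test version gives 99.1, hence 100. Dropout: 100 / (1 − 0.25) = 133.3, against 133 stated. The figure reproduces, and the point below does not affect it.

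**2. Where an event could come to notice after discharge.**

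| Source | IG | CG |
|---|---|---|
| App entry on problems after each session | yes | no |
| Phone calls with the physiotherapist | yes | none described |
| Four clinic visits | yes | none described |
| Health-service use at t2 | yes | yes |
| Fear of falling at t2 | yes | yes |

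The only shared source that can show actual harm is health-service use. As described, it does not name a fall or injury as the cause, it relies on recall over nine months, and it misses falls that led to no treatment. It also misses patients lost before t2 (25% expected, with evaluation of complete cases only).

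**3. Effect of unequal ascertainment.** The capture rates are assumptions. If true risk is the same in both groups, it cancels, and the apparent risk ratio equals capture in IG / capture in CG.
- 90% versus 50%: 0.9 / 0.5 = 1.8. With a true risk of 20%, that is 18% against 10%.
- 90% versus 25%: 0.9 / 0.25 = 3.6.

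**4. Precision if both groups were asked the same questions.** The documents give no fall risk, so a range is assumed. With 100 per group and equal risk p, the 95% half-width for the difference is 1.96 × √(2p(1 − p)/100).
- p = 20%: 1.96 × √0.0032 = 11.1 points
- p = 30%: 1.96 × √0.0042 = 12.7 points
- p = 40%: 1.96 × √0.0048 = 13.6 points
- p = 50%: 1.96 × √0.0050 = 13.9 points

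**5. Power for an excess in the IG, 100 per group, two-sided 5%.**
- 20% vs 30%: 37%
- 30% vs 40%: 32%
- 40% vs 50%: 29%
- 30% vs 50%: 83%

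**6. Rare events, such as serious exercise injuries.** If none were seen and capture were complete, the one-sided 95% upper bound is 1 − 0.05^(1/n). This gives 2.95% for n = 100 and 2.23% for n = 133.

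**The case against.** **The article is a condensed document.** It says events are not expected; it does not say they will go unrecorded. Table 1 is presented as a core set of instruments, and adverse-event procedures may stand in a fuller protocol. This is correct. A reader might infer that no harm will be recorded, and the document does not support that. What can be criticised is the stated reasoning and the outcome set as listed.

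**Screening and a low expected risk fit together.** A reader might call the eligibility criteria and the Data monitoring statement contradictory. They are not: excluding patients at higher risk and tailoring the exercises is a coherent basis for expecting few events. What remains is that the section argues from the absence of a drug and from individual fitting to no expected events, which is further than those premises reach.

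**The remark on movement errors.** The Intervention section says "PD patients are prone to small movement amplitudes during exercise that they cannot perceive and therefore cannot correct by themselves". It is tempting to read this as an admitted hazard of training at home. It concerns the size of movements, that is, quality of execution, and the same section answers it with expert correction at clinic visits. It is not evidence of risk.

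**Events would not come only from the IG.** Treatments, hospital stays and medication are asked of all patients at t0 and t2, so treated harm, including harm treated outside hospital, could surface in either group. The supportable claim is narrower: falls and minor injuries are more likely to be heard of in the IG.

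**The trial is too small to establish safety.** This also stands. Identical items would leave a moderate excess mostly undetected. They would still replace non-comparable anecdote with an estimate and its uncertainty.

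**Conclusion.** The point holds in a limited form. The inference that adverse events are not expected is weakly justified for largely autonomous exercise over nine months, even allowing for the remote monitoring, calls and visits. The listed outcomes contain no fall or injury measure, the shared health-service item is indirect, and opportunities to report differ by group.

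Under assumed capture rates, unequal reporting alone could produce an apparent risk ratio of 1.8 to 3.6 when true risks are equal. Symmetric items would give a difference with a half-width of about 11 to 14 percentage points (assumed fall risks of 20% to 50%, 100 evaluable patients per group) and only 29% to 37% power for a 10-point excess. The gain is description, not proof of safety.

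The primary outcome, the sample size and the decision to have no data monitoring committee are untouched. It is a cheap improvement worth making.

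**What to change.** 1. In the Data monitoring section, replace the statement that adverse events are not expected with one saying that risk is expected to be low, giving screening and tailoring as the reasons, and that events will be recorded.
2. Add identical self-report items on falls, injurious falls and exercise-related injuries to the t0 and t2 questionnaires of both groups.
3. Have the items in place before CG follow-up begins. The CG is recruited first, so items added only for the IG period could not be compared.
4. Seek the same answers from patients who stop the programme or drop out, and do not restrict this summary to complete cases.
5. Log events heard of through the app, calls and visits in the IG separately, and keep them out of the group comparison.
6. Report by group, with confidence intervals, as a descriptive safety outcome.

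The cost is two or three questionnaire items, one results table and slightly more burden on respondents. Limits that remain are nine-month recall, incomplete answers from patients who leave, and low power for a moderate excess; the report should state them.
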